#### Economic Outcome Measures

The economic analysis will determine the cost and potential cost savings of Telepsychology. Comprehensive information will be gathered on 1) telepsychology-related capital expenditures, and 2) patient-related resource utilization over 12 months for all patients in the project. This will allow us to estimate the combined spectrum of investment expenditures and direct in-hospital cost of Telepsychology as well as cumulative health costs over 12 months. In addition, a Markov-type economic model [54], determining transition probabilities between different health states, will be developed to predict flow of funds and event rates over a 12-month period for Telepsychology participants based on outcomes.

### Sample Size Determination and Power Analysis

The primary response variable for sample size calculation is the proportion (%) of patients who respond to treatment. Treatment response is defined as at least a 50% improvement from baseline to post-treatment level on the GDS [percent change from baseline: (baseline-post)/baseline ≥ 50%]. Demonstration of non-inferiority among treatments differs from that of establishing superiority. For a non-inferiority trial, the null hypothesis states that two treatments are non-equivalent, that is they differ by at least a clinically relevant amount, Δ. [55-62]. The approach will be formulated in terms of the one-sided non-inferiority problem [55,60,61,63] because it is of interest only to test that the treatment response (% responders) for the Telepsychology mode of delivery is not too low compared to that for the standard Same-Room mode of delivery. Note that, for non-inferiority trials, the consequence of a false positive (ie, claiming the novel therapy [Telepsychology] is worse than the standard therapy [Same-Room] when it is, in fact, non-inferior) is to keep patients on the standard therapy. Therefore, the Type I error rate, α, can be set higher than in traditional superiority trials (eg 0.1–0.2) [64].

We estimate that the % treatment responder for Same-Room delivery (P) is 0.70. We assume that a maximum clinically unimportant difference in response proportion (Δ, the non-inferiority effect size) is 0.15 between Telepsychology and the standard Same-Room service delivery (upper limit of one-sided 90% confidence interval must not be greater than Δ = 0.15 for the conditions to be declared equivalent). Using the tables of Machin and Campbell [64] and assuming Δ = 0.15, one-sided α = 0.10, P = 0.70, and power = 0.85, we estimate that approximately n_1 _= n_2 _= 100 subjects per condition are needed for overall treatment effects comparisons. If we further assume that 10% of subjects will not have at least one post baseline measurement (i.e. will not be included in the ITT sample), then 112 subjects must be randomized to each treatment group to yield the required sample size for the primary intent-to-treat analyses (n_1 _= n_2 _= 100/group).

For the ITT sample (n_1 _= n_2 _= 100/treatment group) we will be able to estimate the individual (main effects) end of treatment means for each of the continuous clinical and process measures with a precision of ± 0.2 standard deviations. For the primary outcome measure Δ_Δ1 _= Δ_(Post)T_- Δ_(Post)S_, which measures the difference in change from baseline (pre to immediate post treatment) for the continuous outcome domain measures for the telepsychology condition compared to change from baseline for the standard (same-room) condition, we will be able to estimate with a precision of ± 0.3 standard deviation units using 95% confidence intervals for the difference in two means (Δ_(Post)T_, Δ_(Post)S_), where the appropriate standard deviation is the pooled standard deviation for comparing change from baseline for the telepsychology condition versus the standard condition.

Assuming that 20% of subjects will drop out of the ITT sample (n_1 _= n_2 _= 80, assuming equal treatment distribution of dropouts), we will be able to estimate for the completer sample the individual end of treatment means for each of the measures with a precision of ± 0.2 standard deviations, and the difference in change from baseline (pre to immediate post treatment) for the outcome domain measures with a precision of ± 0.3 standard deviation units.

Both the standard deviation and the distribution of costs are presently unknown for the type of patients who will be enrolled in Telepsychology. Thus, it is difficult to obtain a meaningful estimate of the power to detect a difference in CE from any arbitrary value. We propose to determine costs and apply to our economic model after the completion of the study, and then use the bootstrap technique to obtain a 90% Confidence Interval (CI) around the estimated costs. The bootstrap technique is appropriate because, as noted, the distribution of costs for these types of patients is presently unknown.

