### Data Analysis

#### Primary Clinical Outcome

Testing the non-inferiority of the Telepsychology mode of delivery to the standard Same-Room mode in terms of % responders can be carried out through either a confidence interval approach or through a modified hypothesis testing procedure [55-62]. For both approaches, a conclusion that the two modes of delivery are similar in clinical efficacy (non-inferior) requires that the response proportion (% responders) for the standard delivery (Same-Room) cannot exceed by more than Δ the response proportion for the novel delivery (Telepsychology). We assume Δ = 0.15 between the novel delivery and the standard delivery (one-sided non-inferiority). With the confidence interval approach, the upper limit of the one-sided 90% confidence limit for the difference in % responders for the novel delivery (Telepsychology) and the standard delivery (Same-Room) must be 0.15 (Δ) or less to accept the hypothesis of a non-inferior novel treatment. Statistically, this translates into testing a non-zero difference between the treatments, where noninferiority is established by demonstrating that the difference between treatments is less than the maximum clinically unimportant difference in response proportions, Δ[55-57,59,61,62]. The hypothesis testing approach to evaluating equivalency in % responders, with an appropriately adjusted test statistic as described by Dunnett and Gent [56] and Farrington and Manning [57] will also be used.

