## Discussion

Study recruitment commenced in April 2007, with all follow-up assessments associated with the study expected to be completed by June 2010. As of October 2008, 171 participants have been screened and 111 have been randomized. Of the number randomized, 80 have completed Week 4 assessments, 72 have completed Week 8 assessments, 39 have completed Month 3 assessments, and 6 are due to complete Month 12 assessments.

Addressing a significant knowledge gap, this study is a prospective, randomized evaluation of clinical, process, and cost outcomes for a mental health intervention. The study will test the hypothesis that in-home Telepsychology service delivery will be equally effective as a traditional mode (Same-Room). If this study demonstrates telepsychology efficacy is equivalent to Same-Room service delivery, future research and program development will focus on bringing a wide range of specialized mental health services to the homes of veterans and community based outpatient clinics (eg, CBOCs, Veteran Centers) via videoconferencing technology. If Telepsychology non-inferiority and cost-effectiveness can be empirically established, research that examines a range of important system issues, including effectiveness outcomes and service delivery strategies to maximize the accessibility of mental health services for rural veterans can proceed. We anticipate that future research projects would include examination of telepsychology applications for providing individual and group mental health care to people with a range of other mental illnesses. Furthermore, we will also be able to evaluate the association between process and outcome measures in this study, which will have implications for future telepsychiatry efforts, as well as more general treatment outcome efforts with older veteran populations. Thus, while meeting the VA's mission to provide quality health care to all veterans, this project represents an important step in a programmatic line of research, including planned future VA HSR&D applications in mental health service delivery and care coordination to rural and underserved populations.

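### The one-sided non-inferiority rule is sound and correctly powered, but the protocol writes its null without direction and lets a passing result be called equivalence, which the test cannot show

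*Protocol article*

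**What the plan says.** All places are in the protocol article.

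- **Null (Sample Size Determination and Power Analysis).** "For a non-inferiority trial, the null hypothesis states that two treatments are non-equivalent, that is they differ by at least a clinically relevant amount", Δ. No direction is given.
- **Formulation (same section).** "The approach will be formulated in terms of the one-sided non-inferiority problem", and the reason follows: "it is of interest only to test that the treatment response (% responders) for the Telepsychology mode of delivery is not too low" compared with Same-Room.
- **Decision rule (same section).** The "upper limit of one-sided 90% confidence interval must not be greater than Δ = 0.15 for the conditions to be declared equivalent".
- **Decision rule (Data Analysis, Primary Clinical Outcome).** The same one-sided 90% limit and the same Δ lead to acceptance of a non-inferior novel treatment. The section also says that Same-Room response may not exceed Telepsychology response by more than Δ.
- **Companion test (same section).** It is introduced as "The hypothesis testing approach to evaluating equivalency in % responders".
- **Discussion.** Future work is made to depend on this condition: "If this study demonstrates telepsychology efficacy is equivalent to Same-Room service delivery". The Abstract, the Background and the Discussion all put the hypothesis as the two modes being equally effective.
- **Design figures.** Δ = 0.15, one-sided α = 0.10, Same-Room response 0.70, power 0.85, about 100 per arm analysed and 112 per arm randomized.

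**The concern.** One test has two written conclusions. An undirected null of the kind quoted belongs to an equivalence trial: it is rejected only if the difference is shown to lie inside the margin on both sides. The rule that follows checks one side. Someone who applies the Sample Size section literally would report equivalence, while someone who applies the Primary Clinical Outcome section would report non-inferiority, from the same data and the same limit.

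At stake is what the trial may say when it passes. Equivalence is the stronger claim. It appears in a statement of the primary decision rule, and the Discussion uses it as the trigger for extending the service.

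**Working it through.** **Inputs.** Δ = 0.15, one-sided α = 0.10 (z = 1.2816), power 0.85 (z = 1.0364), response 0.70, and 100 per arm analysed, all from the Sample Size section. A true difference of zero is assumed for the power figure. The difference is taken as Same-Room minus Telepsychology, as the Primary Clinical Outcome section requires when it limits how far Same-Room may exceed Telepsychology.

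**Step 1. Reproduce the plan's own figures.**

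- n per arm = (1.2816 + 1.0364)² × 2 × 0.70 × 0.30 / 0.15² = 5.373 × 0.42 / 0.0225 = 100.3. With the Farrington-Manning restricted variance the result is 99.9. The stated figure is about 100.
- Standard error at 100 per arm = √(0.42/100) = 0.0648. Power = Φ(0.15/0.0648 − 1.2816) = Φ(1.033) = 0.849. Exact binomial enumeration of the Wald limit gives 0.848.
- Allowing for 10% loss: 100/0.90 = 111.1, so 112 per arm.

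The sample size and the 85% power are therefore right for the one-sided non-inferiority test.

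**Step 2. Apply the rule where the written null is true on the other side.** Let Same-Room response be 0.70 and Telepsychology response 0.85. The two differ by Δ, so the null as written holds.

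- Standard error = √((0.70 × 0.30 + 0.85 × 0.15)/100) = √(0.3375/100) = 0.0581.
- Probability that the upper limit is at or below 0.15 = Φ((0.15 + 0.15)/0.0581 − 1.2816) = Φ(3.88), which exceeds 0.999. Exact enumeration gives 0.99995.

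Against the undirected null, the rule would thus reject wrongly almost every time on this side, not 10% of the time. Against a null that Same-Room exceeds Telepsychology by Δ or more, the same outcome is a correct rejection.

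**Step 3. Set the conclusions side by side.**

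| Place | Bound checked | Conclusion or label |
|---|---|---|
| Sample Size section, null | none stated | difference of at least Δ, either way |
| Sample Size section, rule | one-sided upper limit | equivalent |
| Primary Clinical Outcome, interval | one-sided upper limit | non-inferior |
| Primary Clinical Outcome, test | one-sided | equivalency |
| Discussion | none stated | equivalent |

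Only the third row pairs the planned bound with a conclusion that it can support.

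**The case against.** The strongest reply is that the intent is plain. The undirected null is worded as a general remark about non-inferiority trials, and the next sentences fix this trial's formulation as one-sided and give the reason. The Primary Clinical Outcome section states the direction, glosses similarity as non-inferiority and ends its interval rule there. The secondary and process analyses are also framed as non-inferiority, and the Discussion itself speaks of establishing non-inferiority. Talk of equal effectiveness in the Abstract and Background can be read as plain language. A Telepsychology advantage mislabelled as equivalence lets no inferior treatment through.

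Most of this stands. It shows that the test is not in doubt and that the remedy is editorial. It does not remove the sentence that attaches equivalence to a one-sided limit, the label on the companion test, or the use of equivalence in the Discussion.

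Two stronger readings are tempting, and the documents support neither.

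- *A reader might infer that power is about 70%, not 85%.* Two one-sided tests within ±0.15 at 0.10 per side would have power 2 × 0.849 − 1 = 0.698 at 100 per arm. But the protocol plans no such procedure and gives no alpha per side for one; at 0.05 per side the figure would be 49.7%. The 85% is tied to one-sided α = 0.10, where it is correct.
- *A reader might cite an observed 70% v 64% being called equivalent.* The limits are 0.06 ± 1.2816 × √((0.21 + 0.2304)/100) = 0.06 ± 0.085, or about −0.025 to 0.145. These lie within ±0.15, so an equivalence test at the same alpha per side would pass too. The example bears on the size of the margin, not on one side versus two.

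**Conclusion.** The point holds as a contradiction in the null and in the declared conclusion of the primary decision rule. The planned one-sided test can support non-inferiority within 15 percentage points and nothing more. With true rates of 0.85 and 0.70 in favour of Telepsychology, the rule would be met more than 99.9% of the time, so meeting it cannot justify the word equivalent.

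The trial is not underpowered for its planned test: power is 84.9% at 100 per arm, assuming 0.70 response in both arms. The error rate for the one-sided aim, the sample size and the pass or fail result are all unaffected. What changes is the claim that a pass permits.

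**What to change.** Keep the test, the one-sided α of 0.10, the margin and the sample size. Then:

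1. In the Sample Size section, write the null with direction: *Same-Room response exceeds Telepsychology response by Δ or more*. This also settles the order of subtraction for the upper limit.
2. In the same section, end the decision rule with *for Telepsychology to be declared non-inferior*.
3. In the Primary Clinical Outcome section, describe the companion test as one of non-inferiority instead of equivalency.
4. In the Abstract, Background and Discussion, replace equivalent and equally effective, where they state what the trial would conclude, with *non-inferior within 15 percentage points*.

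This needs no more patients and no change of analysis. The cost is a narrower permitted claim. Only if the sponsor does intend two-sided equivalence would the size need to be redone. At 0.10 per side, which is an assumption, 85% power within ±0.15 needs 0.42 × (1.2816 + 1.4395)² / 0.0225 = 138.2, or 139 per arm analysed.

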### Data Analysis

#### Primary Clinical Outcome

Testing the non-inferiority of the Telepsychology mode of delivery to the standard Same-Room mode in terms of % responders can be carried out through either a confidence interval approach or through a modified hypothesis testing procedure [55-62]. For both approaches, a conclusion that the two modes of delivery are similar in clinical efficacy (non-inferior) requires that the response proportion (% responders) for the standard delivery (Same-Room) cannot exceed by more than Δ the response proportion for the novel delivery (Telepsychology). We assume Δ = 0.15 between the novel delivery and the standard delivery (one-sided non-inferiority). With the confidence interval approach, the upper limit of the one-sided 90% confidence limit for the difference in % responders for the novel delivery (Telepsychology) and the standard delivery (Same-Room) must be 0.15 (Δ) or less to accept the hypothesis of a non-inferior novel treatment. Statistically, this translates into testing a non-zero difference between the treatments, where noninferiority is established by demonstrating that the difference between treatments is less than the maximum clinically unimportant difference in response proportions, Δ[55-57,59,61,62]. The hypothesis testing approach to evaluating equivalency in % responders, with an appropriately adjusted test statistic as described by Dunnett and Gent [56] and Farrington and Manning [57] will also be used.

In addition to comparing unadjusted % responders between the modes of delivery conditions, it also is of interest to compare % responders, adjusted for putative confounding variables. Possible covariables to be considered for inclusion in these analyses include initial disease severity as measured by baseline GDS or BDI score, use of psychiatric medication, number of other co-morbid conditions, and relevant others as identified though the preliminary descriptive analyses. Two approaches will be used to evaluate non-inferiority of adjusted % responders for the two delivery conditions. The method of Gart and Nam [65] and Nam [59], which involves calculation of a non-inferiority test statistic within strata of potential confounding variables, formulates a score test for a null hypothesis of a common specified clinically relevant non-zero difference in % responders between two treatments for multiple 2 × 2 tables. Because the above procedure may be limited by the number of covariables (number of strata) that can be used, we will carry out a second set of analyses using a multivariable logistic regression model to obtain estimates of adjusted % responding for each treatment delivery condition for a specified set of values for the covariables, and then will apply the methods described above (one-sided confidence intervals and non-inferiority hypothesis testing) to evaluate non-inferiority of the two interventions. The response variable for these analyses is the dichotomous outcome, responder/non-responder to treatment, with missing data from premature exits treated as non-responders. The primary independent variable is treatment condition.

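### The supplementary logistic-adjusted analysis judges a risk difference at one set of covariate values against a 0.15 margin that was set for the overall difference in % responders

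*Protocol article*

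**What the plan says.** In the protocol article, Data Analysis, Primary Clinical Outcome, the margin is a difference between the two arms' response proportions: "We assume Δ = 0.15 between the novel delivery and the standard delivery (one-sided non-inferiority"). The decision rule is that the one-sided 90% upper limit "must be 0.15 (Δ) or less to accept the hypothesis of a non-inferior novel treatment". Dunnett-Gent and Farrington-Manning tests are named alongside it. Sample Size Determination and Power Analysis uses the same overall difference, with a Same-Room response of 0.70.

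The same Primary Clinical Outcome section then adds two covariate-adjusted evaluations. The first is a stratified score test of a common difference. The second, offered because stratification can carry few covariates, is a multivariable logistic model that yields "estimates of adjusted % responding for each treatment delivery condition for a specified set of values for the covariables". The authors "then will apply the methods described above (one-sided confidence intervals and non-inferiority hypothesis testing"). Candidate covariates are baseline GDS or BDI, psychiatric medication, number of comorbid conditions, and others to be found in descriptive analyses. The article does not give the covariate values, does not mention averaging over the sample, and does not name a standard error for the predictions.

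**The concern.** Two things look wrong in the logistic step.

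**Target.** On the logit scale one treatment coefficient serves all patients. On the risk-difference scale the effect then changes with the baseline risk. A prediction at one set of covariate values describes one type of patient, whereas 0.15 was set for the trial population. One fitted model could fall within the margin at one profile and outside it at another.

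**Variance.** The methods named for % responders work on observed binomial counts. A model prediction at a profile has no count behind it, and its variance is not p(1 − p)/n. If those methods were applied literally, the interval would not have its stated coverage.

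At stake is how far the adjusted result can be trusted as support for, or a challenge to, the unadjusted one.

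**Working it through.** **Inputs from the article.** Margin 0.15, one-sided alpha 0.10, power 0.85, Same-Room response 0.70, 100 analysed and 112 randomised per arm.

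**1. The plan's own sample size.** With equal true rates and unpooled variance,
n = (z₀.₉₀ + z₀.₈₅)² × 2P(1 − P) / Δ² = (1.2816 + 1.0364)² × 0.42 / 0.0225 = 100.3 per arm.
This agrees with the stated figure of about 100. Allowing for 10% loss, 100/0.90 = 111.1, so 112. The sample size stands.

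**2. Risk difference by profile at a fixed odds ratio.** Exactly at the margin, 0.70 v 0.55:
OR = (0.55/0.45) / (0.70/0.30) = 1.2222/2.3333 = 0.524.
For Same-Room response p, with odds o = p/(1 − p), the difference is RD(p) = p − OR·o/(1 + OR·o).

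| Same-Room response | Telepsychology response | Risk difference |
|---|---|---|
| 0.90 | 0.825 | 0.075 |
| 0.85 | 0.748 | 0.102 |
| 0.70 | 0.550 | 0.150 |
| 0.60 | 0.440 | 0.160 |
| 0.30 | 0.183 | 0.117 |

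Between 0.70 and 0.60 the shift is 0.010. Between 0.70 and 0.90 it is 0.075, half the margin.

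**3. Consequence for the adjusted conclusion.** The documents give no covariate effects, so these are assumed: one standard-normal covariate x with log odds ratio 0.5, 1.0 or 1.5 per SD, 100 per arm, overall Same-Room response 0.70, 3,000 simulated trials. The true overall difference is 0.15, so non-inferiority should be declared in 10% of trials. For log odds ratio 1.0:

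| Profile | True difference there | P(non-inferior), two-proportion SE | P(non-inferior), delta-method SE |
|---|---|---|---|
| x = −1 | 0.185 | 0.056 | 0.042 |
| x = 0 | 0.174 | 0.065 | 0.055 |
| x = +1 | 0.106 | 0.330 | 0.391 |
| x = +1.5 | 0.074 | 0.702 | 0.759 |

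The last column shows that a correct standard error does not remove the dependence on the profile. With the two-proportion SE, the conclusion differed among five profiles (x from −1.5 to +1.5) in 18%, 65% and 94% of trials for log odds ratios 0.5, 1.0 and 1.5. At the mean profile the true difference was 0.157, 0.174 and 0.195 respectively, so there the error is on the conservative side.

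**4. Variance, if the two-proportion formula is used.** SE = √{[q₁(1 − q₁) + q₀(1 − q₀)]/100}, where q₁ and q₀ are the predictions at the profile. For log odds ratio 1.0 and a true difference of 0:

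| Profile | Two-proportion SE | Delta-method SE | Empirical SD |
|---|---|---|---|
| x = −1 | 0.070 | 0.084 | 0.084 |
| x = 0 | 0.062 | 0.065 | 0.066 |
| x = +1 | 0.045 | 0.035 | 0.035 |
| x = +1.5 | 0.037 | 0.024 | 0.024 |

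The error runs in both directions. It is slight at the mean profile with a weak covariate (0.064 v 0.065 at log odds ratio 0.5).

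**5. After averaging over the sample.** With predictions averaged over all simulated patients and a delta-method SE, P(non-inferior) at a true overall difference of 0.15 was 0.092, 0.102 and 0.102 for the three covariate strengths. At a true difference of 0, power was 0.864, 0.898 and 0.926, against 0.843 to 0.852 unadjusted.

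**The case against.** The strongest reply is that this is not the trial's decision. The article presents adjustment as an addition to the unadjusted comparison, and the logistic model is the second of two adjusted analyses. That stands. A reader might infer that the trial's non-inferiority verdict hangs on a chosen profile; the documents do not support it, because the unadjusted limit against 0.15 is the stated rule.

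Second, a reader might infer that the variance is definitely wrong. The article never says that a binomial variance will be used for predictions. Its Secondary Analyses section applies the same interval approach and the same two test citations to differences in means, where a binomial variance cannot be meant. The wording may therefore denote only a framework, and a model-based standard error would be consistent with it. This stands too, and the variance point is conditional.

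Third, a reader might infer that the covariate values will be picked after seeing results. The text calls them specified, and a fuller plan may fix them, for example at sample means. But fixing them only removes discretion: the result would still be a difference for one patient type.

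Fourth, the large gaps need profiles far from the planned 0.70, and nothing in the article proposes evaluating there. This stands as a limit on size. Prediction at stated covariate values is also a legitimate supplementary summary. It is less suited to judgement against a margin set for the overall difference.

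**Conclusion.** The point holds for the supplementary logistic-adjusted analysis only. It judges a profile-specific risk difference against a margin defined for the overall difference in % responders, so its conclusion can depend on the profile. That follows from the logit link and needs only that the covariates are prognostic. At the fixed odds ratio of 0.524 the shift is about 0.01 between Same-Room responses of 0.70 and 0.60, and reaches 0.075 at 0.90. The simulated error rates rest on assumed covariate effects and should be read as a range.

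The variance problem arises only if the two-proportion interval and tests are applied literally to model predictions. The article leaves this open. The unadjusted primary verdict and the sample size are untouched.

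**What to change.** Keep the planned logistic model. For every randomised patient, predict the probability of response under Telepsychology and under Same-Room, average each over all randomised patients, and take Same-Room minus Telepsychology. Compute a one-sided 90% upper limit by the delta method or bootstrap and compare it with 0.15. The adjusted analysis then addresses the difference for which the margin was set, with a standard error that suits the estimate. Predictions at particular covariate values can still be reported as description.

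The cost is a sentence or two in the analysis plan and a few lines of code. No further data, patients or change to the primary analysis are needed.
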